# Abbreviations

| AE | adverse event |
| --- | --- |
| AIS | acute ischemic stroke |
| eCRF | electronic case report form |
| EDC | electronic data capture |
| EQ-5D | EuroQOL five dimensions questionnaire |
| GCP | good clinical practice |
| IEC | independent ethics committee |
| IRB | institutional review board |
| mRS | modified Rankin Scale |
| MMSE | mini mental state examination |
| NIHSS | NIH Stroke Scale |
| QALYs | quality adjusted life years |
| rt-PA | recombinant tissue plasminogen activator |
| SAE | serious adverse event |
| TOAST | Trial of Org 10172 in Acute Stroke Treatment |
| TTO | time trade off |

# Brief introduction

The stroke is one of the diseases seriously threatening people's health, and has the features of high incidence, high morbidity and high recurrence rate , Acute ischemic stroke (AIS) is the commonest cerebral stroke type, and accounts for about 60%~80%[[1]](#bookmark1) of all cerebral stroke. The patients will not only experience physical dysfunction, but disorders in mental state, social function and other aspects, which would seriously affect their quality of life, and bring a heavy burden on their families and the society..The population monitoring materials issued by Statistical Center of China's Ministry of Health, the annual number of newly-emerging cerebral stroke patients nationwide is about 2 million, the annual number of patients that die of cerebrovascular disease is about 1.5 million, and the number of surviving patients is 5 million to 6 million. Among the surviving patients, about 3/4 of them have the loss of labor abilities to varying extents and severely crippled patients account for 40%[[2]](#bookmark2). Therefore, the scientific and reasonable prevention and timely correct treatment of cerebral stroke are of important significance.

Up to now, in the drug treatment for ischemic cerebral stroke, only the ultra-early thrombolytic therapy and the antiplatelet therapy obtain the support of evidence-based medicine proof. For example, the application of rt-PA for intravenous thrombolysis within 3 hours after onset significantly reduces the risk of patient death and severe disability. The European Cooperative Acute Stroke Study (ECASS-III) indicated that it is safe and feasible for the patients to receive intravenous rt-PA treatment at 3 to 4.5 hours after stroke, and it can improve the patient's prognosis [[3]](#bookmark3). The large-scale clinical study on the urokinase thrombolytic therapy in China indicated that, a total of 465 patients with acute ischemic stroke were included into 51 sites, and the results showed that, the adoption of urokinase thrombolytic therapy within 6 hours after onset was safe and effective[[4]](#bookmark4). Based on the above evidence, currently the guidelines in all countries recommend the thrombolytic therapy as the therapeutic measure (class I evidence); however, the actual proportion of patients that receive thrombolysis is very low. In USA, the thrombolytic therapy rate of patients with stroke does not exceed 3.5%[[5]](#bookmark5) while the intravenous thrombolysis rate of patients with ischemic cerebral stroke in China is expected to be 1%~3%[[6]](#bookmark6), so the majority of patients do not benefit from the thrombolytic therapy. As for the patients that receive non-thrombolytic therapy, there is still no effective treatment method supported by evidence-based medicine proofs.

In China, the situation of the drugs for ALS is particularly complex, and, according to the relevant reports, there are more than 100 types of drugs for the clinical treatment of AIS.The study of the China Quality Evaluation of Stroke Care and Treatment (China QUEST) evaluated the treatment of Chinese patients with ischemic cerebral stroke during the acute stage[[7]](#bookmark7), and the results indicated: 1) 75.9% (3632/4783) of the patients with ischemic cerebral stroke received the treatment of intravenous nerve protects, including Edaravone, Ganglioside, Calf cerebroside ignotin injection, Maleate cinepazide injection, Nicholin and other nerve protective agents. 2) The proportion of cerebral stroke that receive intravenous or oral Chinese herbal medicines is up to 83.1%. There are over 100 kinds of prepared Chinese medicines that are domestically used, such as red sange root, rhizome of Sichuan lovage, puerarin and Angongniuhuang injection. Only the patients that receive thrombolytic therapy are mentioned in China 2011 Guidelines for Diagnosis and Treatment of Ischemic Cerebral Stroke [[1]](#bookmark8)about the combined medication, and the use of anti-platelet drugs such as aspirin should be initiated at 24 hours after thrombolysis. Although the nerve protective agents and Chinese herbal medicines are commonly used in clinical practice, there is no high-quality RCT that can prove their efficacy and safety, and its use is not recommended in guidelines.

The results of internal investigation of our company indicated that, the domestic therapeutic regimen for AIS was mainly combined medications; the proportion of the patients that received three-drug regimen and four-drug regimen was relatively high: for example, the proportion of patients that used Chinese herbal medicine + antiplatelet drug + cerebral circulation improving drug was 40%, and the proportion of the patients that used Chinese herbal medicine + antiplatelet drug + cerebral circulation improving drug + nerve protective agents was 87%. One meta analysis[[8]](#bookmark9) included 145 RCT studies, where the data on the efficacy and safety of a total of 13289 Chinese Patients were collected, the main outcome index was NIHSS score and clinical effectiveness rate, and the results indicated that the efficacy of Edaravone + Kininogenase was superior to that of Sodium ozagrel; Edaravone+ Kininogenase, as well as the Sodium ozagrel + Edaravone are the most efficacious therapeutic regimen, and can improve the nerve functional disorder. The systematic evaluation on Chinese herbal medicine ligustrazine in treating acute ischemic cerebral stroke[[9]](#bookmark10) indicates that, the combination of ligustrazine with conventional therapies can better lower the score of nerve functional defects than the conventional therapies (*MD*=2.49, 95%CI: 1.00, 3.98). There is no clear conclusion on whether which combined drug regimen is the most efficacious on the patients who miss the timing of thrombolysis.

The acute ischemic cerebral stroke is the main cause that leads to the long-term disenabling, thus bring severe economic burdens[[10]](#bookmark11) to society and patient's family. Therefore, the performing of pharmacoeconomic evaluation on the different therapeutic regimens during the acute phase of cerebral stroke and the seeking of one or more kinds of drug therapeutic regimens with a high price/performance ratio which are suitable to the domestic conditions are of a higher social value. In the field of cerebral stroke treatment, currently there is rare prospective pharmacoeconomic evaluation domestically. Unlike the domestic cerebral stroke study fields which often adopt the cost effectiveness analysis (CEA)[[11]](#bookmark12), this study utilizes the cost utility analysis (CUA) for economic evaluation, the quality adjusted life years (QALYs) serves as the health outcome index, and the advantage of this method lies the measurement of life quality and the improvement of life-span (longevity) [[12]](#bookmark13). Considering the original intention of using this study as the registration study as well as the difficulty in expense collection, this study only collects the direct costs during the patient's hospitalization, and does not collect the indirect cost and implicit cost.

To sum up, this objective of this study is to analyze status quo of different drug combinations in the real world, evaluate the efficacy of different drug combination regimens in treating acute ischemic cerebral stroke, and perform cost-utility analysis. It aims to provide reference for a wide range of clinicians when selecting medications to treat acute ischemic cerebral stroke.

**2 Study objective**

Primary study objective:

Analysis of current treatment situation in acute phase of acute ischemic stroke in real-world settings。

Secondary study objectives

(1) Comparison of effects of various drug combinations in treatment of acute ischemic stroke in real-world settings.

(2) Analysis of cost-utility of various drug combinations in treatment of acute ischemic stroke.

(3) Analysis of occurrences of complications and adverse events during treatment in hospital in patients with acute ischemic stroke.

(4) Analysis of effects of TOAST typing on specific therapy regimens in acute phase of acute ischemic stroke.

# 3 Overview of study design

This was a registered, prospective, multi-center clinical study. The study was planned to included 10, 000 patients with acute ischemic stroke (AIS) and record treatment regimens, treatment outcomes and medical expenses during hospitalization in real clinical practice. This study was to collect patients' data through a electronic data capture system (EDC).

According to the recommendations for treatment and follow-up observations in acute phase in the "Guidelines on diagnosis and treatment of acute ischemic stroke in China 2014 (Draft)", the patients with stroke were planed to receive 5 visits, which occurred at admission (baseline assessment, visit 1), 7 days ± 2 days after medication (visit 2), at discharge (visit 3), 90 days ± 14 days after medication (visit 4, outpatient service or telephone follow-up), and 360 days ± 28 days after medication (visits 5, telephone follow-up), respectively. As for the specifics, refer to [Study Flow Chart](#bookmark14).

In the baseline phase, the investigators should verify the inclusion/exclusion criteria, obtain the patients' informed consent, and try to collect the demographic information, past history, onset and admission conditions, and vital signs of the patients; and collect the following data of clinical examination: ECG, laboratory tests (blood routine, blood glucose, blood lipids, hepatic and renal functions, cardiac enzymes, serum electrolytes, coagulation) and imaging findings, and assess Glasgow Coma Scale, NIHSS score, mRS score and EQ-5D Scale. Seven days ± 2 days after medication, the vital signs of the patients were recorded and the NIHSS scores were accessed again. At discharge, the treatment regimen, vital signs, ECG and above laboratory tests results were recorded during hospitalization, and the Glasgow Coma Scale, NIHSS score, mRS score and EQ-5D scale were accessed, and the medical expenses during hospitalization was also collected. On 90 ± 14 days after medication, the recurrence of stroke, survival conditions and re-admissions were collected; the medical expense until this visits since discharge was recorded; and the mRS score, EQ-5D scale and MMSE scale (only applicable for the patients visiting the hospital) were accessed. On 360 days ± 28 days after medication, another telephone follow-up was given again, to ask the patient's health status, access mRS score, EQ-5D scale, and collect medical expenses.

Only the drug combinations during hospitalization and the occurrences of adverse events during the study period were recorded.

If the patient was discharged on 7 ± 2 days after medication, it should be handled as a discharge note at this time.

As the database can last for several years, whenever there is a need to supplement or modify the data, a retrospective modification / amendment can be carried out at any time. According to the inclusion, data tendency and management factors, it is possible that the duration may be longer; therefore, the patients who are preliminarily included and added during the late stage may be followed up after 3 months.

Techpool can terminate this study at any time due to any reason. The physicians participating in the disease registration study is responsible for notifying IRBs and/or ECs about the premature termination of the study.

If necessary, the disease evaluation can be evaluated more frequently. In this study, any valuable information collected at follow-up visit is recorded.

# 4 Study population

The age of the population included into this study is not less than 18 Y, and the diagnosis at admission is acute ischemic cerebral stroke, male or female.

## Inclusion criteria

The patients who satisfy all of the following criteria can be included into this study:

(1) Age≥18 years

(2) In conformity with the diagnosis criteria (draft) of China 2014 Guidelines for Diagnosis and Treatment of Ischemic Cerebral Stroke

(3) The onset time of thrombolytic patients are within the time window of thrombolysis

(4) The onset time of thrombolytic patients are within one week

(5) The patients or legal guardians can understand and sign the informed consent form

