# 5 Treatment regimen

In the study, the doctors can select the specific treatment regimen for cerebral stroke according to the patient's clinical medical history and characteristics of symptoms as well as the China 2011 Guidelines for Diagnosis and Treatment of Ischemic Cerebral Stroke. This study has no limitations on the selection, dose and treatment course of the treatment drugs.

According toChinese Guideline for Diagnosis and Management of Acute Ischemic Stroke2010, The specific treatment on acute ischemic cerebral stroke refers to the intervention with a certain link in the pathophysiological mechanism of ischemic injuries. Examples are given to the following common drugs for illustration:

1. Intravenous thrombolysis drug: rt-PA and urokinase.
2. Anti-platelet drugs: aspirin and Clopidogrel
3. Anticoagulants: including unfractionated heparin, low molecular heparin, ateroid, oral decoagulants and thrombin inhibitor.
4. Volume expansion drug: hydroxyethyl starch, and low molecular dextran.
5. Nerve protective agents: Edaravone, nicholin and ganglioside.
6. Cerebral blood flow perfusion improving drugs: butylphthalide, human urine kininogenase (Urinary Kallidinogenase for Injection).
7. Chinese herbal medicines: Shuxuetong injection, and Danhong injection.

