# 7 Study procedures

**7.1 Baseline phase**

**Visit1 (At admission Day 0)**

- Signing informed consent forms
- Verify the inclusion / exclusion criteria
- Demographic materials (Sex, Age) and medical insurance type
- Visit delay and visits accepted by emergency*

The items with a "*" can be evaluated.

- Past medical history (stroke, hypertension, diabetes, dyslipidemia, coronary heart disease, atrial fibrillation, carotid plaques, and history of tumor), the history of medications during the recent three days, and risk factors*

The items with a "*" can be evaluated.

- Onset and admissiond (Stroke occurrence time, and main symptoms)
- Imaging examination (Cranial CT/MRI and vascular examination)

If possible, the researchers are expected to burn the disks to store the patient's imaging materials (cranial CT / MRI imaging)

- Vital Signs (Body temperature, pulse, respiration and blood pressure)

The changes in body temperature 1 day and 24 hours after the onset need to be collected.

- NIHSS score
- mRS score
- EQ-5D scale
- ECG examination
- Laboratory tests (blood routine, blood glucose, blood lipids, hepatic and renal functions, cardiac enzymes, serum electrolytes, coagulation)
- Concomitant treatment
- Adverse events

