**9.2 Withdraw from the study**

If the patient experiences any of the followings, the patient should withdraw from this study:

- Wrong inclusion of the patient
- Withdrawal of informed consent
- When any other conditions occur, in the investigator's opinions, terminating this trial is to the subject’s best interests
- Lost to follow-up
- Other

The reason and date of withdrawal should be noted in the electronic Case Report Form (eCRF). Upon terminating the study, a last end-point evaluation should be done, except for lost of follow-up.

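### Inclusion criterion (3) makes entry depend on thrombolysis and its timing against an undefined window, so a registry of real practice loses or leaves unclear its off-window thrombolysis cases

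*Protocol*

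**What the plan says.** Under Inclusion criteria (Section 4, repeated in the protocol abstract), eligibility is conjunctive: "The patients who satisfy all of the following criteria can be included into this study". Criterion (3) is "The onset time of thrombolytic patients are within the time window of thrombolysis". Criterion (4) names the same group with a different limit: "The onset time of thrombolytic patients are within one week". Neither criterion gives hours, an agent or a guideline for the window.

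The check is a Visit 1 task, at admission on Day 0 (Section 7.1: "Verify the inclusion / exclusion criteria"). Section 8.3 places the Day 0 assessment before treatment. The specific stroke regimen, which by Section 5 includes rt-PA and urokinase, is recorded at discharge (Section 7.2, Visit 3).

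The abstract calls the study non-interventional. Its primary objective (Section 2) is "Analysis of current treatment situation in acute phase of acute ischemic stroke in real-world settings".

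Section 9.2 lists "Wrong inclusion of the patient" first among the reasons for withdrawal and does not define it. Section 10.2 builds the full analysis set (FAS) from treatment received and one post-baseline efficacy evaluation, with no exclusion for ineligibility.

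**The concern.** A registry that sets out to describe practice should select patients on facts that do not depend on the treatment they get. Criterion (3) does the opposite: for thrombolysed patients only, it filters on how onset relates to a treatment window. Two patients with the same late onset are handled differently. The one who is not thrombolysed can enter; the one who is thrombolysed cannot.

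Three things are at stake:

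- **Pattern of use.** Off-window thrombolysis is part of current treatment, and patients known at entry to be such cases cannot appear.
- **Safety in the subgroup.** Symptomatic haemorrhagic transformation is the first-listed safety index (Section 8.2). If its risk depends on treatment timing, the rate among registered thrombolysed patients will not represent all thrombolysed patients.
- **Consistency between sites.** With no window stated, sites can apply different limits and so register different patients.

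**Working it through.** **1. Does the criterion exclude by treatment?** All criteria must hold, and (3) speaks only of thrombolytic patients. A thrombolysed patient with onset outside the window fails it. An untreated patient with the same onset is not addressed by (3). Read literally, (4) does not address that patient either. Read as a one-week limit for non-thrombolysed patients, (4) still admits that patient up to a week. The unequal handling holds on both readings.

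**2. Is the answer known at the check?** Eligibility is verified on Day 0, before treatment, and the regimen is recorded at discharge. This gives two cases:

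- Off-window thrombolysis already given or planned at entry: the patient is not registered, and no section brings the patient back.
- Off-window thrombolysis given after the check: the patient is already enrolled. Section 9.2 does not say whether this counts as a wrong inclusion, and the FAS definition has no eligibility exclusion. The protocol does not settle the status.

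**3. Is the window defined?** The introduction mentions rt-PA within 3 hours, rt-PA at 3 to 4.5 hours and urokinase within 6 hours. These are background evidence, and no section ties criterion (3) to any of them.

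**4. Size.** The planned 10,000 has no formula behind it (Section 10.1), so there is no calculation to reproduce. It is used here only as a multiplier.

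Inputs from the protocol: N = 10,000; expected national thrombolysis rate r = 1–3% (introduction).

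Assumed, because the protocol gives no figure: off-window share o = 5–20% of thrombolysed patients; haemorrhagic transformation 4% in-window and 8% off-window.

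- Thrombolysed: N × r = 10,000 × 0.01 to 10,000 × 0.03 = 100 to 300.
- Affected: N × r × o = 100 × 0.05 to 300 × 0.20 = 5 to 60, that is 0.05% to 0.6% of 10,000. At o = 30% and r = 3% the figure is 90, or 0.9%.
- Thrombolysis rate if all affected patients are lost: r × (1 − o). For r = 3% this is 3.0 × 0.95 = 2.85% down to 3.0 × 0.80 = 2.4%.
- Haemorrhage rate over all thrombolysed patients: (1 − o) × 4% + o × 8%. At o = 5% it is 3.8 + 0.4 = 4.2%; at o = 20% it is 3.2 + 1.6 = 4.8%. The registry would show 4.0%.
- Sampling error for comparison: the 95% half-width at 4% is 1.96 × √(0.04 × 0.96 / n), which is 2.2 points for n = 300 and 3.8 points for n = 100.

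If the off-window and in-window haemorrhage rates are equal, the subgroup rate is unbiased and only the pattern of use is lost.

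**The case against.** The strongest reply is that (3) tests onset time, not onset-to-needle time. It can be read as an admission check for patients about to be thrombolysed, which Visit 1 can answer. On that reading a patient who passes on Day 0 and is treated late was correctly included. This stands as a possible reading. It weakens the case of removal after enrolment, but eligibility still turns on a treatment choice and patients known to be off-window at entry are still left out.

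Some stronger inferences are tempting, and the protocol does not support them:

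- **That enrolled patients treated off-window are removed by rule.** Wrong inclusion is undefined, Section 9.2 asks for a last evaluation at withdrawal, adverse events are collected throughout, and the FAS has no eligibility exclusion. Their status is open; removal is not prescribed.
- **That the criterion screens out guideline-discordant use.** It names no guideline.
- **That Section 5 is contradicted.** Its statement "This study has no limitations on the selection, dose and treatment course of the treatment drugs" concerns prescribing, not who may be registered. The conflict is with the primary objective.
- **That haemorrhagic transformation is reported only for in-window use.** Sections 8.2 and 10.4 report it for the whole study population and compare groups. At a 1–3% thrombolysis rate, 97–99% of patients fall outside criterion (3).

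It is also fair to say that the haemorrhage shift in the example, 0.2 to 0.8 points, is smaller than the subgroup's sampling error. That limits its weight. It does not justify an entry rule that works against the primary objective.

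**Conclusion.** The point holds as a defect of eligibility design. Criterion (3) conditions entry on thrombolysis and its timing, uses an undefined window, shuts out patients known at entry to be off-window cases, and leaves unclear those treated off-window later. This is at odds with a primary objective of describing current real-world treatment.

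The consequence is limited to the thrombolysed subgroup. Under the assumed 5–20% off-window share, 5 to 60 patients are affected. If all were lost, thrombolysis use would be understated by 5–20% of its value. Bias in the subgroup's haemorrhage rate is possible but depends on an assumed difference in risk. The 90-day mRS endpoint and other whole-cohort results barely change. The 1–3% is a national background figure, so the subgroup at participating sites may be of a different size.

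The change is worth making because it is cheap and touches the primary objective, not because the numbers are large.

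**What to change.** - Rewrite criteria (3) and (4) together as a single limit on time from onset to admission, applied to every patient whatever treatment is given. Deleting (3) alone would leave (4), which as worded sets no onset limit for non-thrombolysed patients.
- State in Section 9.2 that treatment given after enrolment does not make a patient a wrong inclusion.
- Report thrombolysis, and haemorrhagic transformation among thrombolysed patients, overall and by onset-to-treatment time.

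**Cost.** An amendment to two criteria (in Section 4 and the abstract), one sentence in Section 9.2 and one extra tabulation. Stroke occurrence time is already collected at Visit 1 and initial medication time at Visit 3; the team need only confirm that both are captured finely enough to give an interval in hours. The downside is a slightly more heterogeneous thrombolysed subgroup, which the split by time displays.

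The change concerns who is registered. It leaves treatment decisions alone and implies nothing about which thrombolysis window is clinically right.

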**10.1 Determination of sample size**

For a more comprehensive collection of the patient information on the use of various drug combinations, this study protocol is planned to include 10,000 patients with acute stroke.

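### Inclusion criteria (3) and (4) both name thrombolytic patients, so criterion (4) adds nothing and non-thrombolysed patients have no numeric limit on time since onset

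*Protocol*

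**What the plan says.** The list of inclusion criteria in section 4 opens with "The patients who satisfy all of the following criteria can be included into this study", so the criteria apply jointly. Criterion (3) is "The onset time of thrombolytic patients are within the time window of thrombolysis" and criterion (4) is "The onset time of thrombolytic patients are within one week". The abstract carries the same two lines, so it does not correct the wording.

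Nothing else in the protocol supplies a time limit. The population statement in section 4 adds only that "the diagnosis at admission is acute ischemic cerebral stroke, male or female". Criterion (2) requires conformity with the diagnosis criteria of the 2014 Chinese guideline (draft), but the protocol does not reproduce them. The exclusion criteria in section 4.2 do not mention onset time. Stroke occurrence time is recorded at visit 1 (study flow diagram and section 7.1), but no eligibility rule uses it for patients who are not thrombolysed.

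These patients are meant to be in the registry. The introduction says that it is unclear "which combined drug regimen is the most efficacious on the patients who miss the timing of thrombolysis".

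**The concern.** Two onset limits are set for one group and none for the other. The group without a limit is probably most of the registry and is the one the introduction is most interested in.

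Time since onset matters for the outcomes. Visits 4 and 5 are timed from medication, not from the stroke. The primary efficacy endpoint is the proportion with mRS 0-2 at 90 days, and a secondary endpoint is the NIHSS change from baseline to discharge (section 8.1). A patient admitted late has baseline NIHSS and mRS measured further along the course of recovery, and the day-90 assessment falls later after the stroke.

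Comparing drug combinations is the first secondary objective (section 2), and section 5 leaves drug choice to the physician. Section 10.3 compares groups by chi-square or Fisher's exact test, and by ANOVA or Kruskal-Wallis, with no term for onset time. If late presenters tend to receive different combinations, the comparison is confounded by disease time. Sites may also settle the ambiguity in different ways.

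**Working it through.** **1. Does criterion (4) add anything to criterion (3)?** The introduction mentions thrombolysis windows of 3 h and 3 to 4.5 h for rt-PA. For urokinase it says that "the adoption of urokinase thrombolytic therapy within 6 hours after onset was safe and effective". One week is 7 × 24 = 168 h.

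| Window | 168 h ÷ window |
|---|---|
| 3 h | 56 |
| 4.5 h | 37.3 |
| 6 h | 28 |

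Any thrombolytic patient who meets criterion (3) under these windows also meets criterion (4). The limits nest, so (4) is redundant and does not conflict with (3).

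**2. What do the criteria mean for a patient who is not thrombolysed?** Read literally, there are two options.
- Criteria (3) and (4) do not apply and count as met. There is then no numeric onset limit.
- Criteria (3) and (4) are not met. The patient is then ineligible, which contradicts the stated interest in patients who miss the thrombolysis window.

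Only the first option fits the study's purpose, and it leaves this group without a number of hours or days.

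**3. How many patients have no explicit limit?** The inputs are section 10.1, "this study protocol is planned to include 10,000 patients with acute stroke", and the introduction, "the intravenous thrombolysis rate of patients with ischemic cerebral stroke in China is expected to be 1%~3" (per cent). The complement of the rate is applied to the planned number:
- at 3%: 10,000 × (1 − 0.03) = 9,700 without a limit, 300 covered;
- at 1%: 10,000 × (1 − 0.01) = 9,900 without a limit, 100 covered.

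The rate is a cited national figure for intravenous thrombolysis. The protocol gives no forecast for its own sites, so using it here is an assumption. The conclusion is not sensitive to it: at three times the upper figure, 3 × 3% = 9%, there would still be 10,000 × 0.91 = 9,100 patients without a limit.

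**4. What does a late start do to day 90?** If medication starts L days after onset, the nominal visit 4 falls at 90 + L days after onset. At L = 6 h this is 90.25 days, and at L = 7 days it is 97. Without a limit on L there is no stated upper bound, and once L exceeds 14 days the shift is larger than the ±14-day visit window itself. The documents do not give the distribution of L, so the effect on the outcome proportions cannot be computed.

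**The case against.** Four points can be made on the other side.

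- **A qualitative limit exists.** A reader might infer that anyone presenting weeks after a stroke is eligible. The protocol does not support that as a certainty. The admission diagnosis must be acute ischemic stroke, and criterion (2) brings in guideline criteria whose content cannot be checked here. This stands: what is missing is an explicit numeric limit.
- **The 9,700 to 9,900 are not late presenters.** A reader might take nearly the whole registry to be wrongly admitted. The figure counts patients whom no numeric limit governs. The number arriving after one week is not given and may be small. This also stands.
- **The harm is conditional and partly recoverable.** The primary objective is descriptive, and confounding arises only if late presenters are treated differently, for which the protocol offers no evidence. Because onset time is recorded, late presenters can be identified at analysis, and a statistical analysis plan, not shown here, may provide for this. That is fair, but analysis can only identify or set aside such patients. It cannot define who should be enrolled, which the protocol must do.
- **It is probably a translation slip.** The English text has others, such as an mRS of 60 points for death. A dropped 'non-' in criterion (4) is the likeliest explanation, and the visit 1 request for body-temperature changes around the first day after onset suggests that early presentation was expected. It is not the only non-redundant reading, because (4) could have been meant for all patients with (3) as the tighter limit for a subgroup. The documents do not settle which was meant, and sites work from the text they are given.

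**Conclusion.** The eligibility text is wrong as written. Criterion (4) is redundant against every thrombolysis window the protocol mentions, and non-thrombolysed patients have no numeric onset limit in the abstract or in section 4. On the assumption that the cited 1% to 3% national rate holds in this registry, the gap covers about 9,700 to 9,900 of 10,000 patients, while criteria (3) and (4) govern about 100 to 300.

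The resulting bias is possible, but its size is unknown. It depends on how many patients present late and whether their drug combinations differ, and the protocol informs neither. The finding is therefore an error in an operative eligibility rule with a plausible route to confounding. It does not show that late presenters were enrolled or that results are distorted.

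**What to change.** Check criteria (3) and (4) against the source-language protocol and correct both places, the abstract and the inclusion list in section 4, so that the one-week limit explicitly covers non-thrombolysed patients. The sponsor should confirm whether criterion (4) was meant for non-thrombolytic patients, which is more likely, or for all patients.

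Add an eCRF edit check on time from onset, using the stroke occurrence time already recorded at visit 1. Flag any patient enrolled outside the confirmed limit, and report the main tables with and without those patients.

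The cost is a correction to two lines of text, one edit check and one additional set of tables. No new data are needed. The downside is that some late presenters become ineligible.
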